# A digitally supported home-based exercise training program and dietary protein intervention for community dwelling older adults: protocol of the cluster randomised controlled VITAMIN trial

**DOI:** 10.1186/s12877-018-0863-7

**Published:** 2018-08-14

**Keywords:** Ageing, Older adults, Nutrition, Physical activity, Dietary protein intake, mHealth, Persuasive technology, Exercise, Sarcopenia

## Abstract

**Background:**

Increased physical activity and dietary protein intake are promising interventions to prevent or treat the age-related decline in physical performance in older adults. There are well-controlled exercise as well as dietary intervention studies that show beneficial effects on physical performance in older adults. In practice, however, weekly group based exercise or nutritional programs may not be as effective. To optimise these exercise programs for community dwelling older adults, a digitally supported and personalised home-based exercise training program has been designed aiming to improve physical performance in older adults. In addition, a protein intervention in combination with the training program may further improve physical performance in older adults.

**Methods:**

The VITAMIN study will be a cluster randomised controlled trial with three parallel arms. In total, 240 community dwelling older adults (≥ 55 years) participating in weekly group exercise are randomly allocated into: 1) regular weekly exercise program (Control group, *n* = 80), 2) digitally supported personalised home-based exercise training program group (VITA group, *n* = 80) and 3) digitally supported personalised home-based exercise training program group plus dietary protein counselling (VITA-Pro group, *n* = 80). The VITAMIN study aims to evaluate effectiveness of the digitally supported personalised home-based exercise training program as well as the additional value of dietary protein on physical performance after 6 months. In addition, a 12 month follow-up measurement will assess the retaining effect of the interventions. Primary outcome is physical performance measured by the Modified Physical Performance Test (M-PPT) and relevant secondary and observational outcomes include habitual physical activity and dietary intake, body composition, cognitive performance, quality of life, compliance and tablet usage. Data will be analysed by Linear Mixed Models.

**Discussion:**

To our knowledge, the VITAMIN study is the first study that investigates the impact of home-based exercise, protein intake as well as use of persuasive technology in the population of community dwelling older adults.

**Trial registration:**

NL56094.029.16 / NTR (TC = 5888; registered 03–06-2016).

## Background

The world population is ageing rapidly [1]. As society ages, the decline in physical performance among older adults dramatically increases. The decline in physical performance is associated with increased risk of falling, sarcopenia, frailty, reduction of quality of life, institutionalisation, co-morbidity, premature death and increased health care costs [2, 3]. A major cause of decline in physical performance is sedentary behaviour and a lack of physical activity [4], resulting in a strong association with the prevalence of chronic diseases [5, 6]. Interventions that stimulate physical activity, such as exercise training, seem to improve muscle mass, muscle strength and physical performance, which have a major impact on quality of life and prevention of chronic health conditions [7–10].

In the community, several group based weekly exercise programs aimed to improve physical activity in older adults. These programs, however, were not effective to improve physical performance and quality of life [11]. These outcomes may be caused by the low intensity of the exercise, the low frequency (once a week), and a lack of focus on functional exercise such as activities of daily living [ADL] [11, 12]. To optimise these exercise programs, a personalised home-based exercise training program with a higher intensity, at least twice weekly [13], and functional ADL focused exercises may be more effective to improve physical performance. This program may be further optimised by the support of technology such as a tablet computer. The latter tablet computer with application (i.e. m-health) may improve compliance, execution of the exercises and monitoring progression [14–17].

In addition to this home-based exercise training program, adequate dietary protein intake may further improve physical performance in older adults [18–20]. However, no data is available on the impact of protein intake (counselling) during personalised and digitalised home-based training programs in older adults.

Therefore, the present VITAMIN (VITal AMsterdam older adults IN the city) study aims to improve physical performance of community dwelling older adults by a modular approach:A personalised home-based exercise training program to improve frequency and intensity of functional activities of daily living;Digital support of the training program by a tablet computer for compliance and execution of the exercises as well as personalised coaching and monitoring;Personalised dietary protein counselling to support optimal nutritional status to optimise the impact of the training program;

The objective of the VITAMIN intervention is to evaluate the 6 months effectiveness as well as 12 months follow-up retaining effect of the digitally supported home-based exercise training program as well as the additional value of dietary protein on physical performance in community dwelling older adults.

## Methods

### Study design and setting

The VITAMIN study will be a cluster randomised controlled trial with 3 parallel arms. Participants are recruited from existing weekly community based exercise groups, which will be randomly assigned (with use of computer-generated randomisation lists) as clusters to one of the following groups:Regular weekly exercise program (Control group, *n* = 80),Digitally supported home-based personalised exercise training program group (VITA group, *n* = 80),Digitally supported home-based personalised exercise training program group plus dietary protein counselling (VITA-Pro group, *n* = 80).

The full study duration is 12 months. The study comprises four visits: a screening visit (V1), a post-randomisation baseline visit (V2), 6 months outcome visit (V3) and 12 month follow-up visit (V4). For the intervention groups the 12 months period includes a 6 month intervention period with personalised coaching, and a 6 month follow-up evaluation. Figure 1 provides an overview of the study.

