### Procedures

Subsequently, after obtaining a written consent, the participants will be screened (V1) at their community centre or exercise location (20–30 min). The Physical Activity Readiness Questionnaire (PAR-Q) [21], Mini-Mental State Examination (MMSE) [22] and medical and demographical data will be obtained. Afterwards, the study physicians determine the eligibility of the participants and if indicated consult the general practitioner or specialist. The eligible participants from one regular weekly exercise group will be randomised as a cluster in one of the three study groups.

Table 1 provides an overview of the location, content of assessment and duration of data collection per time point. All measurement visits (V2 - V4) take place at the Amsterdam Nutritional Assessment Center (ANAC) at the Amsterdam University of Applied Sciences (AUAS), Amsterdam, The Netherlands. For transport to the study location the participants receive a travel fee.

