**Table 1 Tab1:**
[figure not shown]
Time, location, content, duration of the VITAMIN study

Note: *ANAC* Amsterdam Nutritional Assessment Center, *PAM* physical activity monitor; *Socio-dem* Socio demographic

Before each measurement visit the participant will receive a 3-day dietary record and physical activity diary to complete at home, as well as an accelerometer to complement the physical activity diary. Subjects are instructed to be fasted prior to each measurement.

All procedures of screening, measurements and interventions are performed by an intensively trained team of students from the AUAS courses: Nutrition and dietetics, Physiotherapy, and Exercise Therapy. This multidisciplinary study team is supervised and trained according to the Dutch Medical Research Involving Human Subjects Act, ICH-GCP guidelines and coordinated by teachers/researchers: a blinded study coordinator (JH), an unblinded study assistant (CD) and two blinded teachers/researchers (SM/TD). In addition, two study physicians are responsible for the medical aspects during the study.

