### Assessments

Table 3 provides a detailed overview of the primary and secondary outcomes as well as explorative outcomes at each time point.

**Table 3 Tab3:** Summary of outcome measures during study visits

	Screening V1	Baseline (T0) V2	6 months (T6) V3	12 months (T12) V4
Physical performance measurements				
Modified Physical Performance Test (M-PPT) [28]		X	X	X
6 Minute Walk Test (6MWT) [33]		X	X	X
Timed Up and Go Test (TUG) [34]		X	X	X
Short Physical Performance Battery (SPPB) [36]		X	X	X
Accelerometry with activity diary		X	X	X
Hand Grip Strength (HGS) [37]		X	X	X
Cognitive performance measurements				
Trail Making, Stroop Color Word test, Letter Fluency [38]		X	X	X
Questionnaires				
Physical Activity Readiness Questionnaire (PAR-Q) [21]	X			
Mini-Mental State Examination (MMSE) [22]	X			
3 day food record [39]		X	X	X
RAND-36 item Health Survey (SF-36) [40]		X	X	X
Geriatric Depression Scale (GDS) [41]		X	X	X
Behavioural Regulation In Exercise Questionnaire (BREQ-2) [42]		X	X	X
Body Composition				
Dual-energy X-ray absorptiometry (DXA) [45, 47]		X	X	X
Air displacement plethysmography (ADP) BodPod [44]		X	X	X
Bioelectrical impedance analysis (BIA) [48]		X	X	X
Mid upper arm muscle circumference (MUAMC) [51, 52]		X	X	X
Height / Weight / BMI [51]		X		
Explorative outcome measures				
Medical and demographical data	X	X	X	X
Tablet usage and satisfaction		X	X	X
Compliance			X	X
Sustainability				X

Note: T0 = post-randomisation baseline visit (V2), T1 = 6 months outcome visit (V3), T2 = 12 month follow-up visit (V4). *BMI* Body Mass Index

X: data will be obtained

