#### Primary outcome

The primary outcome is the change in physical performance measured with the Modified Physical Performance Test (M-PPT), between baseline and 6 months [28, 29]. The M-PPT will be performed as an assessment of multiple dimensions of physical function (basic and complex activities of daily living) with different levels of difficulty. The test is well-known in elderly research [30, 31]. The test consists of 9 items [28, 32]; 1. Book lift; 2. Put on and take off a coat; 3. Pick up a coin; 4. Chair rise; 5. Turn 360°; 6. 15.2 m walk; 7. One flight of stairs; 8. Four flights of stairs; 9. Progressive Romberg test. The maximum score is 36; 4 points per item. The test takes approximately 10 to 15 min.

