##### Explorative outcomes

*Socio-demographic characteristics. (self-report data)* During screening (V1) the participants report in the presence of a study team member: Age, sex, marital status, educational level, ethnicity, exercise group participation, dependency (alcohol consumption and smoking).

*Medical status and history.* Medical history and current status on illness, disabilities and diagnoses is reported by the participant during screening (V1). Also previous and current treatments and/or medications and nutritional supplements are reported. Besides this, information about current specialists or therapists is needed for the eligibility check by the study physician. This is reported in guidance of a study team member. If medical status or medication are changed during the study, this will be reported adequately. (E.g. Adverse Event or Serious Adverse Event).

*Evaluation tablet usage.* At V2 the participant fills out a short questionnaire with questions about earlier experiences with electronical devices. At V3 and V4 the new developed tablet computer behaviour will be assessed by questionnaire. Only intervention groups will receive this.

*Compliance.* Participants will be defined as compliant when ≥80% of the personalised home-based exercise training program is completed during the intervention period. This will be derived from the tablet generated database.

*Sustainability*. The home-based exercise training program will be considered sustainable when at least 80% of the participants in groups VITA and/or VITA-Pro still follow 80% of the training program as planned at baseline after 6 month follow up.

The dietary protein counselling intervention will be considered sustainable when at least 80% of the participants in VITA-Pro still ingest 80% of at least 1.2 g/kg body weight. This is measured at 12 months by evaluation with the coach and previous described measurements.

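### The baseline M-PPT is taken after the exercise group is randomised, with no stated masking of the student team that measures it, so knowledge of the arm could enter the primary change score

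*Protocol article*

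**What the plan says.** **Order of events.** Study design and setting lists a screening visit (V1) and then "a post-randomisation baseline visit (V2". The note to Table 3 repeats this: "T0 = post-randomisation baseline visit (V2". Procedures puts allocation after consent, V1 and the physicians' eligibility decision: "The eligible participants from one regular weekly exercise group will be randomised as a cluster in one of the three study groups".

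**Content of V1.** Besides the PAR-Q, "Mini-Mental State Examination (MMSE) [22] and medical and demographical data will be obtained". Table 3 marks the M-PPT at V2, V3 and V4 only.

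**Primary outcome.** "The primary outcome is the change in physical performance measured with the Modified Physical Performance Test (M-PPT), between baseline and 6 months".

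**Who measures.** The text after Table 1 in Procedures states: "All procedures of screening, measurements and interventions are performed by an intensively trained team of students from the AUAS courses". It then names "a blinded study coordinator", two blinded teachers/researchers and one unblinded assistant. It does not say whether the students are masked.

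**Use of baseline.** Planned statistical analyses makes the baseline values covariates only if the groups turn out to be imbalanced.

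**The concern.** A baseline is normally safe from allocation because it is taken before anyone can know the arm. Here that protection is absent by design. The M-PPT is nine performed tasks scored by an observer, up to 4 points each, so the result depends on how hard the participant tries and how the scorer rates borderline performance. Members of a cluster meet weekly and share one allocation, so news of the arm can spread through the group quickly.

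Two routes lead from allocation to the primary result. The first is effort or scoring at V2 that differs by arm. The second is selective loss: a person who drops out on learning the arm, before V2, has no M-PPT at all. No earlier M-PPT exists to show whether such losses differ between arms in physical performance.

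**Working it through.** **1. Is there any M-PPT before allocation?** V1 holds the PAR-Q, MMSE, and medical and demographic data. Allocation follows V1 and eligibility, and V2 follows allocation. Table 3 first marks the M-PPT at V2. So there is none.

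**2. Does the primary outcome use the V2 value?** Yes. It is the V2-to-V3 change. With time, treatment and their interaction as fixed factors, the between-arm difference in change takes the V2 means directly.

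**3. Are the scorers stated to be masked?** Measurements are assigned to the student team, which also delivers the interventions. The roles stated to be blinded are supervisory. The remark in Planned statistical analyses that the SAP is finalised before unblinding concerns the analysis, not the scoring.

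**4. How does a baseline shift travel?** Let the V2 mean in one arm be displaced by b relative to the other, with V3 unaffected.
- Unadjusted change: bias = b in absolute size.
- Baseline-adjusted with slope β: adjusted difference = (difference at V3) − β × (difference at V2), so bias = β × b. With β between 0 and 1 the bias shrinks but is not removed. The documents give no β.
- A displacement repeated equally at V3 cancels in the change score. Only the part that differs between the visits matters.

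**5. Size, for assumed b.** The plan's inputs are a 1.7-point effect, SD of difference 1.75, cluster size 10, two-sided α 0.05 (sidedness assumed), 80% power and 56 per group. First, the plan's figure:
- Without clustering: n = 2 × [1.75 × (1.960 + 0.842) / 1.7]² = 16.6, rounded up to 17.
- The ICC is printed as 2.5, which is not a possible value. An ICC of 0.25 gives a design effect of 1 + 9 × 0.25 = 3.25, and 17 × 3.25 = 55.25, rounded up to 56, which matches. I use 0.25 only for this illustration.
- SE of the difference in change = 1.75 × √(2 × 3.25 / 56) = 0.596.

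Type I error = 1 − Φ(1.960 − b/SE) + Φ(−1.960 − b/SE). Power if the shift works against the intervention = Φ((1.7 − b)/SE − 1.960).

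| Assumed b (points) | Share of 1.7 | Type I error | Power if adverse |
|---|---|---|---|
| 0 | 0% | 5.0% | 81% |
| 0.25 | 15% | 7.0% | 68% |
| 0.5 | 29% | 13.4% | 52% |
| 1.0 | 59% | 38.9% | 22% |

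These rows show sensitivity to b. They do not estimate b.

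**The case against.** **The arm may not be known at V2.** Randomised is not the same as disclosed, and no section says when participants, trainers or assessors learn the allocation. Disclosure could already wait until after V2. This stands, and it limits the point to a risk.

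**The questionnaire argument.** A reader might infer that the arm is openly visible at V2, because Table 3 marks tablet usage there and Explorative outcomes says "Only intervention groups will receive this". That sentence follows the one on the V3 and V4 tablet-behaviour questionnaire and probably refers to it. The V2 questions concern earlier experience with devices, which could be asked in every arm. Table 1 is not shown, so the order of tests within V2 is also unknown. Visibility through a V2 questionnaire is not established.

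**One team is not one person.** A reader might also infer that the same student coaches and scores a participant. The text does not say so. The team spans three courses and has a blinded coordinator and a separately named unblinded assistant, so some masking structure exists. A fuller protocol could hold the division of roles. What remains is that the article lists who is blinded and does not include the people it assigns to measure.

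**Safeguards and size.** Consent and the eligibility decision precede allocation, which guards against selective recruitment, a main worry in cluster trials. It does not cover what happens between allocation and V2. The 0.5-point shift is assumed, and bias could run in either direction. Baseline adjustment, if triggered, would pass on only part of a shift. All of this stands.

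**The 6-month visit.** Masking of scorers at V3 is a separate matter that does not depend on baseline timing, although one change to the rota serves both.

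**Conclusion.** The point holds as a risk created by a stated design choice. The baseline of the primary outcome follows allocation, nothing earlier can replace it, and the article states no masking for the team that measures it. The conditional covariate does not solve this, since it treats an imbalance at V2 as chance when allocation itself may have caused it.

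The documents do not show that bias occurs, in which direction, or how large it would be. The 29% figure and the error rates in the table rest on an assumed shift, an unadjusted change score with V3 unaffected and, for the error rates, an ICC of 0.25. They support only the statement that a shift of a few tenths of a point would matter against a planned effect of 1.7. The change is worth making because it is cheap and protects the primary outcome.

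**What to change.** 1. Complete V2 for all consenting, eligible members of an exercise group before that group's allocation is drawn, or at least before it is disclosed to participants, trainers and assessors.
2. Divide the existing student team so that no student who coaches scores the M-PPT at V2, V3 or V4, and state whether the scorers are masked.
3. For any group already allocated before V2, report by arm how many people left between allocation and V2.

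If disclosure already waits for V2 and the roles are already separate, one sentence saying so resolves the point.

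**Cost.** Each group waits for its last V2 before starting. With an average cluster of 10 that should be a short delay, though the earliest baselines in a group become somewhat older. The student rota has to be divided. No extra visit is needed. Whether present staffing is enough cannot be checked, because the contents of Tables 1 and 2 are not shown.

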**Fig. 1 Fig1:**
[figure not shown]
Schematic overview of study

### Subjects

We aim to recruit 240 community dwelling older adults (≥ 55 years of age). Participants from the Amsterdam region are recruited through: 1. community based weekly exercise programs provided by health care and sports organisations. 2. a mailing to 10.000 addresses of community dwelling inhabitants. All interested older adults participating in community based exercise programs are provided with an additional information package and are asked to visit the study team at their nearby community centre (V1).

The following inclusion criteria apply:

1) older than 55 years of age, 2) willingness of the general practitioner to be notified on study participation, 3) willingness to comply with the protocol in the opinion of the study physician(s), who ensures safety for the participants by screening especially for any condition, medication, or circumstance that might interfere with the study protocol, 4) ability to understand the Dutch language, 5) absence of current alcohol or drug abuse in the opinion of the investigator, 6) absence of cognitive impairment (MMSE ≤15) or 7) absence of knee or hip surgery in the last 6 months.

### Procedures

Subsequently, after obtaining a written consent, the participants will be screened (V1) at their community centre or exercise location (20–30 min). The Physical Activity Readiness Questionnaire (PAR-Q) [21], Mini-Mental State Examination (MMSE) [22] and medical and demographical data will be obtained. Afterwards, the study physicians determine the eligibility of the participants and if indicated consult the general practitioner or specialist. The eligible participants from one regular weekly exercise group will be randomised as a cluster in one of the three study groups.

Table 1 provides an overview of the location, content of assessment and duration of data collection per time point. All measurement visits (V2 - V4) take place at the Amsterdam Nutritional Assessment Center (ANAC) at the Amsterdam University of Applied Sciences (AUAS), Amsterdam, The Netherlands. For transport to the study location the participants receive a travel fee.

**Table 1 Tab1:**
[figure not shown]
Time, location, content, duration of the VITAMIN study

Note: *ANAC* Amsterdam Nutritional Assessment Center, *PAM* physical activity monitor; *Socio-dem* Socio demographic

Before each measurement visit the participant will receive a 3-day dietary record and physical activity diary to complete at home, as well as an accelerometer to complement the physical activity diary. Subjects are instructed to be fasted prior to each measurement.

All procedures of screening, measurements and interventions are performed by an intensively trained team of students from the AUAS courses: Nutrition and dietetics, Physiotherapy, and Exercise Therapy. This multidisciplinary study team is supervised and trained according to the Dutch Medical Research Involving Human Subjects Act, ICH-GCP guidelines and coordinated by teachers/researchers: a blinded study coordinator (JH), an unblinded study assistant (CD) and two blinded teachers/researchers (SM/TD). In addition, two study physicians are responsible for the medical aspects during the study.

